### **Data Analysis**

The primary endpoint of estimating the proportion difference of children given antibiotic prescriptions in the control versus the DEP arms can be analyzed using a generalized linear mixed model (GLMM). The response is binary (yes or no), and we will treat provider and clinic as random, while accounting for the time period in order to estimate the treatment effect. All data analyses will be conducted in R. For the physician satisfaction end point, we will use characteristic tables to summarize the results of the survey.

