## Research Design and Methods

**Strategic Plan Overview:** This is a randomized crossover study, where clinicians will be randomized to periods where they will use a rehydration calculator application with or without the DEP. The crossover will include a washout period to reduce carryover effect. The study will be conducted over a 9-week period. We will use a random number generator to randomize clinicians to DEP or control arm for the first 4 weeks. After the first 4 weeks, there will be a 1-week washout period without decision support, after which each clinician will cross-over to the other arm for the next 4 weeks.

The DEP algorithm involves entry of clinical variables (age, bloody diarrhea, Breastfeeding, vomiting, mid-upper arm circumference- MUAC). The output provides the probability that the cause of the diarrhea is viral.

The DEP will be integrated as a feature into a Rehydration Calculator application that has previously been tested as part of two clinical studies in Bangladesh (icddr,b/ IEDCR; Khan AI et al, submitted 2019 and Haque et al. PLoS NTD 2017). The Rehydration Calculator with the DEP turned 'off' will serve as a control. The experimental arm of the study will have the DEP turned 'on'. The Rehydration Calculator is an electronic decision-support tool that provides recommendations for rehydration based on entry of age, gender, weight, and dehydration status. Given the outcome measures of this study, the Rehydration Calculator will be configured to not give antibiotic recommendations.

**Study Sites:** 4 Healthcare Facilities in Mali. ( CSRef CV, ASACOSAB1, CSRef CVI, ASACOYIR)

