### Clinical setting:

The clinical approach will adhere to World Health Organization guidelines for the management of uncomplicated diarrhoeal disease in children with No, Some and Severe dehydration. These guidelines have previously been adapted to a digital format (e.g. Rehydration Calculator) and evaluated in a pilot and cluster randomized controlled trial (icddr,b/ IEDCR; Khan AI et al, submitted 2019 and Haque et al. PLoS NTD 2017); clinically relevant outcome measures in these studies were equivalent or improved with digital decision-support. The Rehydration Calculator version to be used in this study will include unchanged weights estimations and oral and intravenous (IV) fluid calculations; changes will include elimination of the antibiotic recommendations and replacement with the viral diarrhea probability. 15 physicians across 4 facilities will be enrolled.

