## a. Detailed Research Methods

### c.i. Study design.

This is a randomized crossover study, where clinicians will be randomized to periods where they will use a rehydration calculator application with or without the DEP algorithm. The crossover will include a washout period to reduce carryover effect. The study will be conducted over a 9-week period. We will use a random number generator to randomize clinicians to DEP (use of the etiology calculator) or control arm (use of a previously-tested rehydration calculator) within site for the first 4 weeks. After the first 4 weeks, there will be 1-week washout period without decision support, after which each clinician will cross-over to the other arm for the next 4 weeks.

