#### c.iii. Data collection

**Clinicians:** We will use a screening form (Appendix 3) and questionnaire (Pre- and post-Study) to collect quantitative (Appendix 4 & 5) data regarding clinician attitudes and experiences using the App and its role in diarrheal management. These questionnaires will be administered by study coordinators at 2 time points: 1) at the start of the study, and 2) at the end of the study. We will also use the App itself to collect data regarding physician usage.

**Children:** For each enrolled patient, study staff will collect:

- At enrolment, demographic and clinical variables
- At discharge, hospital outcome measures, including intravenous and oral fluids, and antibiotics, zinc administered
- At 10-days post-discharge, health outcomes including persistence of diarrheal and abdominal symptoms, returns to healthcare, and medication use since discharge, will be collected over a phone call.

**Instruments:** As mentioned, electronic tools that are compliant to the protections of PHI (Protected Health Information) will be used in this study. These include the Outbreak Responder software, which includes the DEP, and if needed, RedCap.

**Data Storage:** Data collected on Outbreak Responder software will be stored on a secure cloud-based server (server is physically based in Singapore; this is a HIPAA compliant server managed by Amazon Web Services).

Access to the server(s) will be restricted and the server management conforms to industry standard for health information.

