### **Sample Size Calculation and Outcome (Primary and Secondary) Variable(s)**

For estimated 90% of children receiving antibiotics in control arm (per mHDM study), and estimated 80% of children receiving antibiotics in DEP arm, along with a within- and between- period correlations for each physician of 0.15, a sample size of 360 children (**15 clinicians**, with 2 cross-over periods and 12 patients during each period) will achieve a power above 95% to detect a 2-sided significance of 0.05. If enrolment is reached prior to the pre-determined study period, enrolment will be continued until the end of the study period; this is important given that aspects of the study outcomes are dependent on weeks of use.

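### The plan names a difference in proportions as the primary quantity but gives no step from the planned mixed model to it, and leaves out baseline predictors already collected

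*Protocol*

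**What the plan says.** The Data Analysis section names the primary quantity as "The primary endpoint of estimating the proportion difference of children given antibiotic prescriptions in the control versus the DEP arms" and, in the same sentence, says that it "can be analyzed using a generalized linear mixed model (GLMM"). For this yes/no response, "we will treat provider and clinic as random, while accounting for the time period in order to estimate the treatment effect". The section states no link function, no conversion from coefficients to a difference, and no baseline covariate.

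The sample size section works on the same scale, with 90% prescribing under control and 80% under the algorithm.

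Under c.i. Study design, it is clinicians who are randomised, "within site for the first 4 weeks", and each then crosses over. The Clinical setting section says "15 physicians across 4 facilities will be enrolled". Under c.iii. Data collection, staff record for each child "At enrolment, demographic and clinical variables". The section on individual privacy confirms that the clinical data include bloody stool and vomiting.

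**The concern.** A logistic mixed model estimates the change in log odds for a given clinician. When clinicians differ and prescribing is near 90%, that is neither the marginal odds ratio nor the difference on which the trial is sized. The difference can be recovered in more than one way, and the ways disagree. If the rule is not fixed beforehand, the headline number depends on an analyst's choice made after the data are in.

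The second part is smaller. Randomisation sets the order of conditions for a clinician; it does not allocate children. Which children a clinician sees in each four-week block is left to circumstance. A crossover with a period term removes stable clinician differences and common time trends, but not differences in case mix between one clinician's two blocks. Variables that could absorb some of this are recorded before treatment and are not in the model.

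**Working it through.** **Inputs from the protocol.** Control 0.90, algorithm arm 0.80, within- and between-period correlation 0.15, 15 clinicians × 2 periods × 12 children = 360 (180 per condition), two-sided 0.05.

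**The plan's own power figure.** The cluster-crossover design effect is 1 + 11 × 0.15 − 12 × 0.15 = 0.85. The standard error is √[0.85 × (0.09 + 0.16)/180] = 0.0344, so power is Φ(0.10/0.0344 − 1.96) = Φ(0.95) ≈ 83% (82.4% with a pooled variance). The stated figure, above 95%, does not reproduce. That is a separate matter; 83% is only the baseline here.

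**Effect measures for 90% against 80%.**
- Marginal difference: −10.0 points. Risk ratio: 0.80/0.90 = 0.889.
- Marginal odds ratio: (0.8/0.2)/(0.9/0.1) = 0.444.

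**What a logit mixed model targets.** Take logit p = β + u with u normal, SD σ. Choose σ so that Var(p)/[p̄(1 − p̄)] = 0.15, and choose β in each arm so that the average of p over u is 0.90 or 0.80 (numerical integration). The protocol does not say at which rate the 0.15 applies, so three are shown.

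| 0.15 matched at | σ | β control, β algorithm | Conditional odds ratio | p at u = 0 | Difference at u = 0 |
|---|---|---|---|---|---|
| 90% | 1.31 | 2.792, 1.807 | 0.373 | 0.942, 0.859 | −8.3 points |
| 85% | 1.16 | 2.681, 1.730 | 0.387 | 0.936, 0.850 | −8.6 points |
| 80% | 1.07 | 2.615, 1.685 | 0.395 | 0.932, 0.844 | −8.8 points |

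Averaging p over u returns −10.0 points in every row, by construction. If 0.15 were instead a latent-scale correlation (an assumption), σ = √[(0.15/0.85) × π²/3] = 0.76, the odds ratio is 0.42 and the difference at u = 0 is −9.4 points.

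**Simulation.** 400 trials were simulated with 15 clinicians in 4 sites, randomised within site, σ = 1.31, and 20% of the random variance at site (assumed). The difference standardised over the random effect averaged −10.1 points (SD across trials 4.0). The zero-random-effect figure, taken in period 1, averaged −9.1. The two rules thus differ by about 1 to 2 points, less than the sampling error but systematically.

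**Site.** In the same simulations, power was 82.0% with fixed site effects and 82.3% with no site term at all. Median standard errors were 0.356 and 0.358, and the two treatment estimates correlated 0.998.

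**Covariates.** As a linear approximation, multiply the variance by 1 − R². The protocol gives no R², so these values are assumed:
- R² = 0.03: standard error 0.0338, power 84.0%.
- R² = 0.06: standard error 0.0333, power 85.1%.
- R² = 0.10: standard error 0.0326, power 86.6%.

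For plausibility, suppose 20% of children have bloody stool and all of them are treated (both assumed). The rest are then treated at (0.90 − 0.20)/0.80 = 0.875 under control and (0.80 − 0.20)/0.80 = 0.75 under the algorithm. The explained share is 0.16 × 0.125²/0.09 = 2.8% and 0.16 × 0.25²/0.16 = 6.3%. Bloody stool alone would therefore add about 1 to 2 points of power.

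**The case against.** The protocol names no link. An identity link would give a difference directly, and a logit fit can be standardised to one, so the model is compatible with the stated quantity. Link and post-estimation steps, like covariates, often sit in a statistical analysis plan, and none is at hand.

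Most of this stands, and it sets the limits of the point. What remains is that the protocol fixes both quantity and model in one sentence without joining them. The identity link is also a doubtful way out. At 90% prescribing with σ = 1.31, about 47% of control clinician-periods of 12 would have every child treated, so fitted probabilities press against 1.

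A reader might infer more than the documents support:
- *The model cannot give the difference, or an odds ratio will be the headline.* Nothing says so.
- *The effect would look much larger than it is.* An odds ratio set beside a difference compares two scales. On one scale the gap is 0.37 to 0.39 against 0.44, and the zero-random-effect shortcut understates the difference.
- *The randomisation strata are left out.* Site is the only stated stratum, and clinic is in the model as a random effect. A variance from 4 levels is poorly estimated, but treatment is contrasted within clinician and hence within site.
- *Adjustment would rescue power.* With little outcome variance at 80% to 90% prescribing, an R² of 10% to 20% is optimistic. The protocol presents the algorithm's inputs as predictors of viral cause, not of prescribing, and it documents no case-mix imbalance.

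**Conclusion.** The point holds as a gap in specification. The declared quantity and the planned model need a stated step between them, and the choice of step moves the result from −10 points to about −8.3 to −8.8 under the sample-size assumptions. These figures rest on a logit link, a normal random intercept, and 0.15 read as a correlation on the proportion scale.

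The missing covariates are an inexpensive improvement rather than an error. The gain is about 1 to 4 points of power for an assumed R² of 0.03 to 0.10, and more if case mix differs between clinician-periods. Random rather than fixed site effects are not a defect.

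**What to change.** Keep the mixed model and state the logit link. Add age, bloody diarrhoea and vomiting as pre-specified fixed effects beside treatment and period. Take them from the staff enrolment record in both conditions, not from the application: with the algorithm off, the calculator's listed inputs do not include stool blood or vomiting.

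Declare as the primary result the marginal risk difference. Predict each enrolled child's probability under both conditions, average over children and over the estimated random-effect distribution, and subtract. Name the interval method in advance, for example a bootstrap resampling clinicians or a delta-method interval that respects clinician clustering. Give the conditional odds ratio as supportive. Replace the permissive verb with a firm commitment to this analysis. Fixed site effects are optional.

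The cost is a few sentences and a few lines of R, with no new data. The downside is a few degrees of freedom and possible sparse cells at 80% to 90% prescribing, so the covariate list should stay short.

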### **Data Safety Monitoring Plan (DSMP)**

A Data and Safety Monitoring Plan (DSMP) will be made for the study. It will provide the overall framework for the research protocol's data and safety monitoring. Adverse events (anticipated or unanticipated) will be reported to the DSMB/ERC within 24 hours for severe adverse events (SAE), with independent reports submitted to all participating DSMB committees.

### **Direct Access to Source Data/Documents**

The investigator/institutions will permit (by way of written agreement) trial-related monitoring, audits, DSMB review, and regulatory inspection; providing direct access to source data/documents.

### **Assessment of Safety**

All adverse events which are observed actively or reported/volunteered by subject/guardian will be recorded with information about severity (i.e., whether mild, moderate or severe) and possible relation to the study intervention by the study physician. In case of any serious adverse events, the investigator will notify DSMB immediately by telephone/facsimile/email within 24 hrs and take appropriate measures to safeguard the participants. Every SAE must be reported, even if the Investigator considers that it is not related to the intervention. The Completed serious adverse event (SAE) form should be submitted to DSMB within 72 hours either by fax, or by email.

### **Definitions of Serious Adverse Events (SAE) and Adverse Events:**

**Serious Adverse Event:** Any adverse event that results any of the following outcomes: death, significant disability/incapacity, and/or life-threatening situation of any patient within the study period (enrolment of patient at admission to 10 days after discharge).

**Adverse Events:** An adverse event will be defined as an untoward medical event temporally associated with a medical intervention in a patient that does not necessarily have a causal relationship with the treatment.

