### Background of the Project including Preliminary Observations:

Diarrhoeal diseases are a leading cause of morbidity and mortality in children worldwide, with an estimated one billion cases and 500,000 deaths annually. While the majority of deaths due to diarrhoea occur in lower-income countries, infectious diarrhoea remains a significant problem in high-income countries. Aside from the immediate morbidity, potential long-term sequelae of diarrhoea in children in low-resource settings include malnutrition, growth faltering, and deficits in cognitive development.

While the cornerstone of diarrhoeal disease management in children is rehydration, a number of other management decisions, including the use of antibiotics and laboratory testing, may impact the course of disease. Overuse of antibiotics may cause side-effects and lead to increased antimicrobial resistance in the community. Underuse of antimicrobials for some bacterial and protozoal pathogens may lead to prolonged duration of illness and facilitate transmission. This can result in increased days of school or parental work missed, and among malnourished children in resource-poor settings, potential for growth faltering or death. Overuse of laboratory testing may have financial impact on both the patient and the healthcare system, and underuse may delay appropriate therapy or prevent recognition of outbreaks. Thus, accurate and cost-effective determination of diarrhoea etiology is important for proper case management in children and for public health.

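### The serious adverse event list omits later admission, readmission and prolonged stay, and *severe* and *serious* are mixed, so prompt reporting of a non-life-threatening readmission to the DSMB is not assured

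*Protocol*

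**What the plan says.** Four parts of the protocol bear on this.

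- **Definitions of Serious Adverse Events (SAE) and Adverse Events.** An SAE is "Any adverse event that results any of the following outcomes: death, significant disability/incapacity, and/or life-threatening situation of any patient within the study period", and the window is "enrolment of patient at admission to 10 days after discharge". There is no hospitalisation criterion and no residual category for other medically important events.
- **Assessment of Safety.** "In case of any serious adverse events, the investigator will notify DSMB immediately by telephone/facsimile/email within 24 hrs". A completed form follows within 72 hours, and "Every SAE must be reported, even if the Investigator considers that it is not related to the intervention". Other events have only a recording duty: "All adverse events which are observed actively or reported/volunteered by subject/guardian will be recorded with information about severity", graded mild, moderate or severe, with an assessment of relatedness.
- **Data Safety Monitoring Plan (DSMP).** "Adverse events (anticipated or unanticipated) will be reported to the DSMB/ERC within 24 hours for severe adverse events (SAE". A separate plan is announced but is not part of the document at hand.
- **c.iii. Data collection.** Ten days after discharge, persistent symptoms, "returns to healthcare, and medication use since discharge, will be collected over a phone call".

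The hypothesis states that the algorithm will reduce inappropriate antibiotic use safely. The background section says what withholding antibiotics can do: "Underuse of antimicrobials for some bacterial and protozoal pathogens may lead to prolonged duration of illness". It also names transmission and, in malnourished children in poor settings, growth faltering or death.

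**The concern.** The intervention shows clinicians a probability that the diarrhoea is viral, and the hoped-for effect is fewer antibiotic prescriptions. The corresponding risk is a bacterial infection left untreated after a high viral probability. The protocol's own figures make some such cases plausible. The cross-validated AUC is about 0.85, and *Shigella* was found in 2–43% of children with watery diarrhoea in the multicentre study it cites.

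Severely malnourished children and those with severe pneumonia, severe sepsis or meningitis are excluded. For the children who remain, one foreseeable course is an illness that lasts longer or worsens enough to bring the child back for admission without threatening life. That event falls outside the SAE list. A monitoring board that relies on expedited reports could therefore learn of it late, and the plan does not say when.

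**Working it through.** No sample size, power or event count enters this point, so there is no stated figure to reproduce. The check follows one type of event through each reporting rule.

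**Step 1: is it an adverse event?** Yes. The adverse event definition is broad and requires no causal link. Worsening illness that leads to readmission falls under it, and Assessment of Safety requires it to be recorded if it is observed or reported by the guardian.

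**Step 2: is it an SAE?** Only if it is fatal, disabling or life-threatening. The index admission is not in question, because the window opens with enrolment at admission. The gap concerns three events: admission after the index encounter, readmission, and a prolonged index stay.

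**Step 3: which deadline applies?**

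| Event within the window | SAE by definition? | Assessment of Safety: 24 h notice, 72 h form | DSMP section: 24 h |
|---|---|---|---|
| Readmission, life-threatening | Yes | Yes | Yes |
| Readmission, not life-threatening or disabling, graded severe | No | No | Depends on the reading of *severe* |
| The same, graded moderate | No | No | No |
| Prolonged index stay, not life-threatening or disabling | No | No | Only if graded severe, and on one reading |

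**Step 4: can the wording of the DSMP section be settled from the text?** Not fully. The abbreviation list expands SAE as a *serious* event, which suggests that *severe* is a slip. On that reading the second and fourth rows have no deadline anywhere. Taken literally, *severe* is the top intensity grade in Assessment of Safety. A readmission graded severe would then be due within 24 hours under one section while not being an SAE under another. On either reading, a readmission graded moderate has no deadline.

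**Step 5: does the follow-up call close the gap?** The call takes place 10 days after discharge, which is also the end of the SAE window, and it asks about returns to healthcare. The information will therefore exist for families who are reached. The protocol states no rule by which an admission reported on the call becomes a safety report.

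**The case against.** The strongest reply is that the SAE list is not the only safety channel. The DSMP section can be read as sending adverse events in general to the DSMB or ethics committee. Assessment of Safety has every observed or volunteered adverse event recorded. Direct Access to Source Data/Documents permits DSMB review of source records. Resolution of diarrhoeal symptoms at 10 days is a secondary outcome and bears directly on prolonged illness, the harm the background names first. The separate monitoring plan, not shown, may link the call to reporting and provide tables by arm.

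Most of this stands, and it limits what can be claimed. A reader might infer that a readmission would never reach the DSMB, or that the safety part of the hypothesis could not be monitored at all. The routes just listed contradict both. An SAE definition governs expedited reporting; it does not decide whether the arms can be compared for safety. A reader might also infer that readmission is the most likely serious harm. The background does not mention admission, and no rate is given, so that would be an assumption.

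The reply does not supply a deadline. Permission to inspect source data is not a duty to report, recording an event is not notification, and a secondary outcome is analysed rather than expedited. The monitoring plan may add rules, but it would have to work around a definition that the protocol itself fixes too narrowly and a trigger that it words in two ways.

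Two practical objections also stand. The protocol gives no expected length of stay against which prolongation could be judged, and a trigger at the call can come days after the event. The fix has to allow for both.

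**Conclusion.** The point holds as a defect in the expedited reporting rule. The closed SAE list omits admission after the index encounter, readmission and prolonged stay, and the sections on reporting use *severe* and *serious* for what appears to be the same trigger. Prompt DSMB notice of a non-fatal, non-disabling, non-life-threatening readmission after antibiotics were withheld is therefore not assured. Such an event may still be recorded and reach the DSMB later.

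The documents contain no admission or readmission rate, so the number of affected children cannot be estimated, and the conclusion does not depend on one. It rests on the SAE list being exhaustive as written and on the unseen monitoring plan not overriding it. The trial can run as designed. The correction is worth making because the hypothesis includes safety and the change is cheap.

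**What to change.** 1. Add to the SAE definition: unplanned hospital admission or readmission after the index encounter, or prolongation of the index stay. State that the index admission itself does not count. Define prolongation in advance and apply it in the same way in both arms, since clinicians know whether the algorithm is switched on.
2. Reconcile the Data Safety Monitoring Plan, Assessment of Safety and Definitions sections. Use *serious* for the reporting trigger throughout and keep *severe* for the intensity grade only.
3. Have the existing 10-day call trigger an SAE form whenever a return to healthcare led to admission.
4. Tabulate these events by arm for the DSMB.

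The cost is one line in the definition, one trigger on the call form, consistent wording in three sections and a few more SAE forms. One limitation remains: an event found only at the call will be reported with delay, by up to 10 days if it occurred soon after discharge. No treatment rule changes.
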